## Abstract

**Background:**

Proximal femoral fractures are strongly associated with morbidity and mortality in elderly patients. Mortality is highest among frail institutionalized elderly with both physical and cognitive comorbidities who consequently have a limited life expectancy. Evidence based guidelines on whether or not to operate on these patients in the case of a proximal femoral fracture are lacking. Practice variation occurs, and it remains unknown if nonoperative treatment would result in at least the same quality of life as operative treatment. This study aims to determine the effect of nonoperative management versus operative management of proximal femoral fractures in a selected group of frail institutionalized elderly on the quality of life, level of pain, rate of complications, time to death, satisfaction of the patient (or proxy) and the caregiver with the management strategy, and health care consumption.

**Methods:**

This is a multicenter, observational cohort study. Frail institutionalized elderly (70 years or older with a body mass index < 18.5, a Functional Ambulation Category of 2 or lower pre-trauma, or an American Society of Anesthesiologists score of 4 or 5), who sustained a proximal femoral fracture are eligible to participate. Patients with a pathological or periprosthetic fractures and known metastatic oncological disease will be excluded. Treatment decision will be reached following a structured shared decision process. The primary outcome is quality of life (Euro-QoL; EQ-5D-5 L). Secondary outcome measures are quality of life measured with the QUALIDEM, pain level (PACSLAC), pain medication use, treatment satisfaction of patient (or proxy) and caregivers, quality of dying (QODD), time to death, and direct medical costs. A cost-utility and cost-effectiveness analysis will be done, using the EQ-5D utility score and QUALIDEM score, respectively. Non-inferiority of nonoperative treatment is assumed with a limit of 0.15 on the EQ-5D score. Data will be acquired at 7, 14, and 30 days and at 3 and 6 months after trauma.

**Discussion:**

The results of this study will provide insight into the true value of nonoperative treatment of proximal femoral fractures in frail elderly with a limited life expectancy. The results may be used for updating (inter)national treatment guidelines.

**Trial registration:**

The study is registered at the Netherlands Trial Register (NTR7245; date 10-06-2018).

## Background

Proximal femoral fractures are amongst the most common fractures in the elderly [1] with the incidence rate increasing with age. In the Netherlands 20,000 patients are admitted with a proximal femoral fracture to the hospital each year [2, 3]. This number is expected to rise because of our ageing society. Approximately 20% live in a nursing home prior to the fracture. Proximal femoral fractures result in activities of daily living (ADL) dependence and increased morbidity, strongly diminishes the patients’ (health-related) Quality of Life (QoL) and total health care costs [4–7].

A proximal femoral fracture is also strongly associated with mortality. Over 30% of patients die within the first year and 8–13.3% die within the first month [8–10]. Mortality is highest among elderly with both physical and cognitive comorbidities [9, 10]. A 36 and 55% mortality rate within 6 months after fracture has been reported for institutionalized patients and patients with advanced dementia, respectively [11, 12]. This shows that the hip fracture is merely a symptom of the frail status of these patients and the start of cascade breakdown at the end of life.

Operative treatment allows early mobilization, is effective in pain relief, and is believed to prevent secondary complications like pneumonia, urinary tract infection, and pressure sores. However, surgery will not prevent frail patients from developing aforementioned complications. Instead, patients may develop additional surgical complications like bleeding, infection, and non-union, necessitating further (operative) interventions [13]. Hospital admission after a proximal femoral fracture itself can provoke cognitive impairment or delirium in these patients who often live in delicate equipoise in an institutionalized setting.

Although surgery is considered a good analgesic option, it is not the only analgesic option. Moreover, surgery also has disadvantages. It is questionable whether surgery is beneficial in terms of quality of life and whether surgery is satisfactory for family and caretakers involved. The World Health Organization (WHO) definition for palliative care supports a holistic approach in facing life-threatening illness, which is a proximal femoral fracture in a frail elderly patient. Randomized trials comparing operative and nonoperative management in institutionalized elderly are scarce, due to ethical issues, and focus on mortality instead of quality of life.

Guidelines have no strict advice for frail elderly with a proximal femoral fracture, as a result of lack of evidence on palliative care in these patients. The National Institute for Health and Care Excellence (NICE) advises to discuss if patients are open to hospital admission and possible surgery [14]. Dutch guidelines advocate operative treatment in patients with a life expectancy beyond 6 weeks [2, 15]. This leads to practice variation. Current practice is that over 90% of femoral fracture patients that presented to hospital are operated, even if they are institutionalized and have a limited life expectancy [16].

A systematic review of the literature on nonoperative management versus operative management of proximal femoral fractures in frail elderly resulted in 7 studies that met the eligibility criteria [17–24]; All were nonrandomized, five were retrospective studies. A total of 1189 patients were included, 242 (20.3%) were treated nonoperatively. The mean age ranged from 76.9–101.8 years. The data indicated an unadjusted pooled odds ratio of 3.95-fold and 3.84-fold higher 30-day and 1-year mortality for nonoperative versus operative management. Data also showed that mortality was affected by the number of comorbidities. None of the comparative studies examined (health-related) quality of life, degree of frailty, and costs. The literature review shows a lack of high quality evidence on the true effect of nonoperative versus operative management on quality of life, pain, mortality, complications, and costs in the first 6 months after trauma in frail institutionalized elderly. Those answers are needed to aid patients and health care providers in decision-making for surgical repair, particularly in frail elderly patients. The above shows that the best treatment is not known, and supports the need for high quality evidence. Evidence supporting (non)operative management in terms of quality of life, pain, complications, and mortality is lacking.

It is common practice to decide on treatment following a shared decision process, but still nonoperative treatment is uncommonly used. It is unclear to what extent patients or their relatives currently have a say in the treatment decision.

This study aims to investigate the effect of nonoperative management versus operative management of proximal femoral fractures in a selected group of frail institutionalized elderly with regards to quality of life and clinical outcomes. Treatment decision will be reached following a structured shared decision process, in which pros and cons of both operative and nonoperative management are discussed with patients, their relatives, and all relevant care providers involved.

## Methods/design

### Aim of the study

This study aims to investigate the effect of nonoperative management versus operative management of proximal femoral fractures in a selected group of frail institutionalized elderly on the quality of life, level of pain, rate of complications, time to death, satisfaction of the patient (or proxy) and the caregiver with the management strategy, and health care consumption.

### Study design and setting

This study will be a two-arm non-randomized (observational) multicenter cohort study and an economic evaluation alongside. The study will be conducted with a non-inferior design. Relevant societies for surgery (Dutch Association of Surgery (NVvH), Dutch Association of Trauma Surgery (NVT), Dutch Orthopaedic Association (NOV), and Dutch Association of Orthopaedic Surgery (NVOT)), clinical geriatrics (Dutch Association of Clinical Geriatrics (NVKG)), elderly care (Association of Elderly Care Physicians (VERENSO)), the Dutch Patient Federation, and two committee members of the Dutch guideline for treatment of proximal femoral fractures are represented in the study team. Patients will be recruited from several hospitals throughout The Netherlands. The following 26 hospitals will participate: Albert Schweitzer Ziekenhuis, Alrijne Ziekenhuis, Amphia Ziekenhuis, Amsterdam UMC (location VUmc), Bernhoven, Catharina Ziekenhuis, Deventer Ziekenhuis, Dijklander Ziekenhuis (location Westfriesgasthuis), Dijklander Ziekenhuis (location Waterland Ziekenhuis), Elisabeth TweeSteden Ziekenhuis, Erasmus MC, Flevo Ziekenhuis, Isala, Maasstad Ziekenhuis, Meander MC, Noordwest Ziekenhuisgroep, OLVG, Radboud UMC, Rijnstate, Rode Kruis Ziekenhuis, St. Antonius Ziekenhuis, Streekziekenhuis Koningin Beatrix, Tergooi, Ziekenhuis Gelderse Vallei, Ziekenhuis Tjongerschans, and Zorggroep Twente.

The study has started in September 2018. The recruitment period will be 24 months, with a follow-up of 6 months. The results of the study are expected mid-2021.

### Study registration

The study is registered at the Netherlands Trial Register (NTR7245; date 10-06-2018).

### Study population and eligibility criteria

This study focuses on frail institutionalized elderly who have a limited life expectancy and fracture their proximal femur. In order to be eligible to participate in this study, a subject must meet all of the following criteria:
Frail institutionalized elderly person (i.e., 70 years or older, living in a nursing home pretrauma, who either:
is malnutritioned (i.e., cachexia or a Body Mass Index, BMI, of < 18.5 kg/m^2^); orhas mobility issues with increased risk of falling pretrauma (i.e., Functional Ambulation Category (FAC) 2 or less) *; orhas severe comorbidities (American Society of Anesthesiologists (ASA) class 4 or 5).Acute proximal femoral fracture, confirmed on X-ray or CT-scanProvision of informed consent by patient or proxy

* The FAC is a functional walking test that evaluates ambulation ability [25, 26]. This 6-point scale assesses ambulation status by determining how much human support the patient requires when walking, regardless of whether or not they use a personal assistive device. FAC category 2 are patients who require manual contact of no more than one person during ambulation on level surfaces to prevent falling, consisting of continuous or intermittent light touch to assist balance or coordination. Patients categorized as 0 (nonfunctional ambulatory), 1 (dependent for continuous and necessary physical assistance) to 2 due to a temporary and easily resolvable problem will not be eligible.

A potential subject who meets any of the following criteria will be excluded from participation in this study:
Bilateral proximal femoral fracturesPeriprosthetic fractureFracture diagnosed more than 7 days after traumaPatients with a known metastatic disease and a confirmed pathological fracture of the proximal femurInsufficient comprehension of Dutch language to understand rehabilitation programs and other treatment information (this applies to the person signing consent, being either the patient or proxy)Participation in another surgical intervention or drug study that might influence any of the outcome parameters

### Treatment of participants

#### Shared decision process

The decision for type of treatment (operative or nonoperative) is achieved by shared decision making (SDM). Shared decision making is based on determining the goals of care for the patient [27]. The purpose of goals of care is to safeguard patients who are unlikely to benefit from operative treatment, especially in patients in the palliative or terminal phase. Goals of care discussion with these frail elderly patients, or in case of cognitive impairment, with a proxy at the onset of proximal femoral fracture are useful in shared decision making. Although some form of SDM is also used in current practice, this study will use a much more structured approach towards this process. Prior to start of treatment, patients will be informed in an objective and structured way about what either treatment arm of the study involves and what complications may occur in either treatment arm. Both for nonoperative and operative management, a full forecast is given verbally and on paper. Combined with the preferences and objections of the patients or their proxy, this is the starting point of a shared decision process. All principal health care providers (i.e., a trauma or orthopedic surgeon, elderly care physician, and geriatrician if possible) as well as the patient and his/her relative(s) or legal representative will take part in this shared decision process. The patients perspective will play a key role in the decision process.

#### Nonoperative management group

The intervention group will be subjected to nonoperative management of the proximal femoral fracture. This group is referred to as nonoperative group. The aim is to transfer patients back to their nursing home location as soon as reasonably possible after treatment decision has been made. Treatment is focused on patient comfort and consists of pain control (often using opioids), with breathing support and physical therapy and occupational therapy consultation (for optimal lying and sitting position) as deemed necessary by the multidisciplinary treatment team. Anti-decubitus mattresses beds and other measures to prevent or treat complications will be used as needed. Progression of comorbidities will also be monitored closely. The general strategy and outline for treatment will be the same for all patients. However, as treatment needs to be tailored to the individual patient’s needs, standardization of treatment is not possible. Relevant details of treatment will be registered for possible use in the statistical analysis.

#### Operative management group

Patient opting for operative treatment, will have operative management of the proximal femoral fracture (if no medical contra-indications or objections by treating physician). The choice of implant will depend on the fracture type, and will adhere to the Dutch guideline for hip fracture treatment [2]. In general, intracapsular femoral neck fractures will be fixed with a (hemi)arthroplasty or screw fixation, and extracapsular pertrochanteric fractures with a dynamic hip screw, dynamic compression screw, or an intra-medullary fixation. Perioperative care will be according to local hospital protocols in order to have a real-life situation. As soon as reasonably possible after surgery, patients will return to their nursing home for further (palliative) care. The principles for palliative care are the same as described for the nonoperative group. Relevant details of treatment will be registered for possible use in the statistical analysis.

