### Recruitment and informed consent

Eligible persons presented to the Emergency Department (ED) with a proven proximal femoral fracture will be informed about the study in the ED or upon admission at the surgical or geriatric ward. After an explanation of the study, they will receive written information and a consent form from the attending physician, the clinical investigator, or a research assistant. Patients meeting all inclusion criteria and none of the exclusion criteria will be recruited in the hospital within 48 h after hospital admission. Should patients not be able to sign informed consent themselves, a legal representative (proxy) will receive verbal and written information about the study by the attending physician, the clinical investigator, or a research assistant, and will be asked to consent with participation of the patient. After signing informed consent by patient or proxy, the shared decision process will be carried out using a structured approach. This will result in identifying the primary treatment that is deemed best for the individual patient. Participation in this study is on a voluntary basis. If patients (or proxy on their behalf) do not wish to participate, they can do so without specifying why. Deciding not to participate in the study will not affect regular treatment and follow-up care. Participants are allowed to withdraw from the study at any time after they have given their written consent.

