### Statistical analysis

Data will be analyzed using the Statistical Package for the Social Sciences (SPSS) version 24.0 or higher (SPSS, Chicago, Ill., USA) and will be reported following the STrengthening the Reporting of OBservational studies in Epidemiology (STROBE) guidelines. Normality of continuous data will be tested with the Shapiro-Wilk test. Homogeneity of variances will be tested using the Levene’s test. A two-sided *p*-value < 0.05 will be taken as threshold of statistical significance in all statistical tests. The analysis will be performed on a per-protocol basis, (as that is the most conservative approach) and verified by an intention-to-treat analysis if needed. Patients who have died will remain in the analysis as censored. If necessary, missing values will be replaced using multiple imputation following the predictive mean matching method, using ten imputations.

Descriptive analysis will be performed in order to report the outcome measures and other variables collected for the entire population as well as per treatment group. Continuous data will be reported as mean and SD (if Normal) or median and quartiles (if non-Normal), categorical data as number with percentage.

Univariate comparison between the groups will be done using Student’s T or Mann-Whitney U-test (for Normal and non-Normal data, respectively), or Chi-squared test or Fisher’s Exact test (categorical data, as applicable). The Student’s T-test will be done with equal variance assumed or not assumed, based upon the results of the Levene’s test.

For the primary outcome measure, a non-inferiority margin of 0.15 points for mean EQ-5D scores was chosen because it is reasonable and on the border of what would be considered a clinically important effect. The null hypothesis in the non-inferiority framework is that nonoperative management is inferior to operative management with regards to the EQ-5D score. This hypothesis will be tested through the adjusted contrast between the two interventions at 6 months. Specifically, the 95% confidence interval of the estimated contrast will be examined, and if the limit of the interval is less than the threshold value of 0.15 points, non-inferiority of nonoperative management to operative management at 6 months will be concluded.

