Multivariable analysis for continuous outcome measures that are repeatedly measured over time will be done using generalized estimating equations (GEE) for longitudinal analysis on a per-protocol and intention-to-treat basis to investigate the effect of treatment. In the primary GEE model, the primary outcome variable studied (quality of life on EQ-5D) will be analyzed as a dependent variable, using treatment (nonoperative versus operative) as between subjects variable and time as within subjects variable. The interaction term of group and time (group x time) will be assessed, to evaluate whether the change over time differed between groups. Analyses will be corrected for baseline differences and all models will be corrected for center of inclusion. Repeatedly measured continuous secondary outcome variables will be analyzed using similar GEE models. Continuous outcome measures only ones and dichotomous secondary outcome measures will be analyzed using multivariable linear regression models and logistic regression models, respectively.

Subgroup analysis are planned for patients with an intracapsular or extracapsular fracture.

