## Discussion

Treatment guidelines for proximal femoral fractures are mainly focused on regaining function and independence in activities of daily living. Other considerations may apply to frail elderly with a limited life expectancy, for whom comfort and pain are particularly relevant. Whether or not operative treatment is needed in this respect is undecided. This study aims to investigate the value of nonoperative management versus operative management of proximal femoral fractures in a selected group of frail institutionalized elderly with a limited life expectancy.

There are some limitations to this study. First, selection bias could be a factor in this study, since patient or proxy opting for nonoperative management may arguably be in worse condition with regards to their pre-trauma condition and comorbidities. A randomized controlled trial (RCT) would have avoided selection bias, however randomizing patients with a limited life expectancy was considered unfeasible (and unethical) by the research team. Patient recruitment in trials randomizing between operative and nonoperative treatment is known to be challenging, and would likely introduce an unacceptably high level of selection bias; surgeons with clear preference for a particular treatment may be unwilling to inform patients about the study, and patients (or their proxy if patient is unable to decide) with preference for a particular treatment will not sign informed consent. The chosen observational design allows all centers and all patients to participate, and real-life data will be collected. For patients with severe cognitive impairment, informed consent will be obtained by their health care proxy. That makes the current study design the most feasible to investigate this issue. As a second limitation, it could be argued that the questionnaire completed by proxy may differ from the patients rating, however since the majority of this study population is expected to suffer from cognitive impairment, questionnaire completion by proxy will be inevitable. Finally, at least 26 hospitals will participate, and treatment protocol and shared decision processes may vary across sites. This may introduce some heterogeneity, but also makes the results more generalizable.

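### Eligibility does not require that both treatments are open to the patient, and patients who cannot have surgery are assigned to no group, so the contrast may mix management with fitness for surgery

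*Protocol article*

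**What the plan says.** All references are to the protocol article.

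- **Study population and eligibility criteria.** The list opens with "In order to be eligible to participate in this study, a subject must meet all of the following criteria". It covers age, nursing-home residence, one marker of frailty (one of the three is ASA class 4 or 5), an acute fracture and consent. Neither the inclusion nor the exclusion criteria ask whether surgery is medically possible.
- **Recruitment and informed consent.** The order is fixed: "After signing informed consent by patient or proxy, the shared decision process will be carried out using a structured approach".
- **Shared decision process.** "The decision for type of treatment (operative or nonoperative) is achieved by shared decision making (SDM"). The surgeon, the elderly care physician and, if possible, the geriatrician take part with the patient and relatives.
- **Operative management group.** A patient who opts for surgery "will have operative management of the proximal femoral fracture (if no medical contra-indications or objections by treating physician").
- **Nonoperative management group.** The group is described by management alone: "The intervention group will be subjected to nonoperative management of the proximal femoral fracture". The reason for nonoperative care plays no part in the description.
- **Statistical analysis.** "The analysis will be performed on a per-protocol basis, (as that is the most conservative approach"), with intention-to-treat as a check if needed. On confounding: "Analyses will be corrected for baseline differences and all models will be corrected for center of inclusion".
- **Discussion.** Selection is acknowledged in one form: "patient or proxy opting for nonoperative management may arguably be in worse condition with regards to their pre-trauma condition and comorbidities".

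**The concern.** Taken together, these sections allow a patient to be enrolled for whom surgery is not an option, or who opts for surgery after consent and does not get it. There are only two groups, and nothing says in which of them, or in which analysis set, that patient belongs. As treated, the patient can only be nonoperative.

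The study is meant to inform decisions between the two managements and to feed into guidelines. If the nonoperative group combines patients who chose that course with patients who had no alternative, the contrast compares more than management. It also compares patients fit for surgery with patients who were not. This applies to the 6-month EQ-5D contrast on which non-inferiority rests, and at least as much to mortality, complications and costs, where early events count in full.

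The selection acknowledged in the Discussion runs through the choice of patient or proxy. Selection through medical contra-indication or physician objection, which the operative-group section itself introduces, is not mentioned.

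**Working it through.** **Step 1: can such a patient be enrolled?** Yes. No criterion concerns operability, severe comorbidity is one way into the study, and consent precedes the decision.

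**Step 2: where is the patient analysed?** The article does not say. For a patient who opted for surgery but did not receive it, three readings are possible:

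| Reading | Effect on the contrast if these patients do worse |
|---|---|
| Counted as nonoperative (as treated) | Lowers nonoperative EQ-5D; works against non-inferiority |
| Counted as operative (by intention) | Lowers operative EQ-5D; makes non-inferiority easier to show |
| Dropped from the per-protocol set | Removes these patients, but those with no surgical option who accepted nonoperative care remain |

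The direction therefore depends on a rule that is not stated.

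**Step 3: can the planned correction repair it?** In part. ASA grade, Charlson index, FAC and KATZ-ADL are collected and can be used. They describe frailty and comorbidity, not whether surgery was open. Where no patient of the same kind was operated on, the model can only extrapolate.

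**Step 4: possible size.** The plan states no figure for this, so there is none to reproduce. Let f be the share of the nonoperative group without a surgical option, and d the amount by which their EQ-5D is lower than that of the rest of the group. Counted as nonoperative, they shift the contrast by f × d. Both inputs are assumptions. The margin of 0.15 is from the Sample size calculation section.

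| f | d = 0.10 | d = 0.20 | d = 0.30 |
|---|---|---|---|
| 10% | 0.01 (7% of margin) | 0.02 (13%) | 0.03 (20%) |
| 20% | 0.02 (13%) | 0.04 (27%) | 0.06 (40%) |
| 30% | 0.03 (20%) | 0.06 (40%) | 0.09 (60%) |
| 40% | 0.04 (27%) | 0.08 (53%) | 0.12 (80%) |

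These are shifts before adjustment, among patients who contribute an EQ-5D score. Correction for baseline would reduce them. Early deaths also matter: the plan treats patients who die as censored and tests at 6 months, so if the sickest die early the shift at 6 months may shrink or reverse.

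**Step 5: what a moderate shift would mean.** Inputs from the Sample size calculation section: SD 0.30, 50 per arm. The standard error is 0.30 × √(2/50) = 0.06. Power against the stated 95% confidence interval rule, with no true difference, is Φ(0.15/0.06 − 1.96) = Φ(0.54) = 71%. With a shift of 0.04 against nonoperative care it is Φ(0.11/0.06 − 1.96) = Φ(−0.13) = 45%. (The starting value is 71% rather than the stated 80% because 50 per arm gives 80% only at a one-sided 5% level. That is a separate matter and does not affect this point.)

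**The case against.** A fair defence has five parts.

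1. **Physicians are parties to the shared decision.** A contra-indication or objection raised there belongs to the process and need not be a veto outside it. This stands, and it narrows the case in which the per-protocol and intention-to-treat sets diverge to patients who opted for surgery and then did not receive it. It does not give the others a surgical option.
2. **The chance of surgery is rarely exactly zero.** Physician objections may differ between clinicians and across 26 hospitals, so a patient refused at one site might be operated on at another. That is ordinary confounding by indication, which adjustment can partly address. This stands: a complete lack of operated counterparts holds only for absolute contra-indications, and ASA class 5 alone does not prove one.
3. **The stated aim concerns frail institutionalized elderly, not only those with a choice.** The Discussion defends a design open to all centers and all patients. This stands as a reason to keep the whole-cohort analysis. It does not tell the reader how much of that contrast is fitness for surgery.
4. **Mitigation exists.** Comorbidity measures are collected, as are treatment goals and details of the decision, and models are corrected for baseline and center. True, but the listed decision details name neither operability nor the reason for nonoperative care, and no analysis is tied to them.
5. **Assignment to analysis sets may be left to a fuller document.** That may be so for fine detail. The eligibility list and the condition on surgery are both fixed in this article, and the problem arises from combining them.

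A reader might go further and infer that refused patients are counted as nonoperative by shared decision and that the comparison is therefore biased. The article does not support this: it assigns them to no group, and neither the presence nor the direction of bias can be established from it.

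**Conclusion.** The point holds in limited form. The protocol neither requires that both treatments are open to the patient nor says how patients without a surgical option, or who opted for surgery and did not receive it, are classified and analysed. The contrasts may therefore mix the effect of management with fitness for surgery, and the planned correction can only partly separate the two.

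The size is unknown. The range of 0.01-0.12 (7-80% of the margin) runs from trivial to serious and rests wholly on assumed shares and differences, before adjustment and ignoring early deaths. The direction is also open. This is a change that should be made, because it is cheap and the information cannot be recovered reliably later; it is not a demonstrated bias.

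**What to change.** 1. On the shared decision form, before the decision, record whether both options were medically open and offered. Record also the reason whenever treatment is nonoperative.
2. State how a patient who opted for surgery but did not receive it is classified in the per-protocol set and in the intention-to-treat set.
3. Pre-specify the non-inferiority contrast and the main secondary comparisons in patients with both options open, at least as a key sensitivity analysis beside the whole cohort.
4. Report patients with no surgical option separately and descriptively.

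**Cost.** One or two form fields and a few sentences of text. The restricted analysis loses nonoperative patients and precision. Starting from 50 evaluable per arm with SD 0.30, unadjusted, the 95% interval half-width is 1.96 × 0.06 = 0.118. If 20% of the nonoperative group is set aside (40 against 50), it is 1.96 × 0.30 × √(1/40 + 1/50) = 0.125. If 40% is set aside (30 against 50), it is 1.96 × 0.30 × √(1/30 + 1/50) = 0.136.

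Whether both options were open is itself a judgement that may vary by site, which is a reason to show the whole-cohort result alongside. None of this sets a rule on who should be operated on.
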